## Abstract

**Introduction::**

The incidence of type 2 diabetes has been increasing year by year in recent years. Type 2 diabetes is an important risk factor in the occurrence and development of heart failure, and it is the second potential risk factor after coronary artery disease. At present, there is no unified etiology, pathogenesis, and syndrome differentiation criteria for type 2 diabetes with chronic heart failure, and it is susceptible to subjective factors. Therefore, standardized, objective, and standardized research is needed to provide reference and guidance for clinical diagnosis and treatment. In this study, the theory of syndrome differentiation is used to initially explore the distribution of traditional Chinese medicine syndromes in patients with type 2 diabetes and chronic heart failure through case data collection, syndrome extraction, and clinical data analysis.

**Methods/design::**

In this study, we will collect at least 500 cases of type 2 diabetes with chronic heart failure that meet the standard outpatient and hospitalization, and fill out the case information collection form. Then we will collect a number of clinical diagnosis and treatment information, and judge the syndrome based on the sum of the contribution of each syndrome to the relevant syndrome. We will use Microsoft Excel to establish a database, enter the relevant diagnosis and treatment, and syndrome information of the case information collection table, and verify and correct in time to ensure the accuracy of the data.

**Discussion::**

This study will provide reference and guidance for the clinical diagnosis and treatment of type 2 diabetes with chronic heart failure.

**Trial registration::**

ClinicalTrials.gov, ChiCTR2000033010, Registered on May 18, 2020.

## Introduction

1

In recent years, the incidence of diabetes mellitus (DM) has increased at an alarming rate. There are about 1.2 million diabetic patients in China every year, and about 90% of them are type 2 DM (T2DM).^[1]^ T2DM is an important risk factor in the occurrence and development of heart failure,^[2,3]^ and it is the second potential risk factor after coronary artery disease.^[4]^ Its associated insulin resistance, hypertension, dyslipidemia, age, obesity, and infection are also risk factors for heart failure.^[5]^ Once heart failure occurs in DM patients, the mortality rate will increase 10 times, and the 5-year survival rate is only 12.4%.^[6]^ In addition, heart failure is also an independent risk factor for T2DM. About 15% to 35% of nondiabetic heart failure patients can develop DM, which leads to an increase in new-onset DM.^[7]^ Clinically, the morbidity and mortality of T2DM combined with chronic heart failure (CHF) are increasing year by year, which seriously affects the survival rate and quality of life of patients. It is a problem worthy of attention in the current clinical frontline. T2DM patients due to coronary artery disease, hypertension, cardiomyopathy, diabetic microangiopathy, abnormal extracellular matrix formation, endothelial dysfunction, renin angiotensin system and sympathetic nervous system activation, insulin resistance and other factors, and complex mechanisms. The synergistic effect of a wide range of comorbid or complicated cardiovascular diseases leads to fibrosis, necrosis, and even apoptosis of cardiomyocytes.^[8]^ Both primary myocardial damage (diabetic cardiomyopathy) and ischemic myocardial damage (combined with coronary heart disease and myocardial ischemia) can promote the occurrence and progression of heart failure, so its incidence and prevalence are both significantly higher than nondiabetics. In addition, heart failure is also an independent risk factor for T2DM.^[7]^ After heart failure occurs, the body activates the sympathetic nervous system and the renin-angiotensin-aldosterone system through the mechanism of neurohumoral regulation, which aggravates insulin resistance and increases blood glucose; increased catecholamine concentration in myocardial tissue causes cardiomyocyte apoptosis; blood vessels. Overexpression of angiotensin II and excessive production of aldosterone can promote myocardial collagen synthesis and accelerate the formation of myocardial fibrosis, which in turn aggravates heart failure and forms a vicious circle.^[9]^ Traditional Chinese medicine (TCM) holds that CHF combined with T2DM is a compound disease syndrome, and its pathogenesis is complicated and intertwined, and the syndrome types are complicated and change. Due to the influence of DM factors, it has its own particularity. Modern medicine has increasingly perfected the understanding of the etiology, pathogenesis, energy metabolism, and other aspects of T2DM combined with CHF, and standardized treatment programs have made great progress. However, there are no special effective measures for the prevention and treatment of the disease, and there are certain limitations that cannot meet the growing health needs of patients. TCM treatment T2DM combined with CHF has flexibility and diversity. Compared with single-component chemical preparations, various components of TCM compound can cooperate with each other to play a therapeutic role. TCM belongs to multitarget, multichannel, and multilink comprehensive treatment. To achieve the purpose of controlling blood sugar, regulating blood lipids, preventing, and treating myocardial fibrosis, and improving cardiac function.

At present, the research on the etiology and pathogenesis, syndrome type, clinical efficacy, etc, of this disease is mostly concentrated on the research level of single disease, and few diseases are involved. Regarding the understanding of the etiology and pathogenesis of CHF, TCM holds that it is a combination of the deficiency and the truth, and it is often combined with phlegm and drinking. Qi deficiency and blood stasis are the basis of heart failure syndrome.^[10]^ Some studies^[11,12]^ have shown that the heart disease is mainly heart, lung, and kidney. T2DM combined with CHF is a complex disease, its pathogenesis and syndrome types are complex and diverse, and the manifestations of syndromes at different stages of the disease are very different. The relevant literature reports on this type of heart failure are very low, and there is a lack of research on syndromes. Clinical diagnosis and treatment of this disease are mostly based on personal experience and simple case summary. Moreover, there is a big difference from the common CHF patients in symptom performance and syndrome differentiation treatment. At present, there is no unified etiology, pathogenesis, and syndrome differentiation criteria for T2DM combined with CHF, and it is susceptible to subjective factors. Therefore, standardized, objective, and standardized research is needed to provide reference and guidance for clinical diagnosis and treatment. The syndrome differentiation system advocated by [name]^[13]^ is based on the syndrome differentiation theory, which distinguishes syndromes based on syndromes and the combination of syndromes and syndromes to form a syndrome-certification Dialectical thinking process. Syndrome is the pathologic essence determined by the identification of syndromes and is the key to syndrome differentiation. In this study, the theory of syndrome differentiation is used to explore the distribution rules of TCM syndromes in patients with T2DM and CHF through case data collection, syndrome extraction, and clinical data analysis. We will explore the relationship between syndromes and disease influencing factors, summarize the basic pathogenesis of the disease, and provide a certain theoretical basis and scientific guidance for clinically reasonable and standardized treatment. We aim to play a positive role in the standardization, standardization, and internationalization of TCM.

## Methods/design

2

### Study design and settings

2.1

This study will be conducted at the Kailuan Majiagou Hospital and Tangshan Hospital of Traditional Chinese medicine (Tangshan City, Hebei Province). This protocol was written and based on Standard Protocol Items: Recommendations for Interventional Trials guidelines. The participants will be informed about the research, procedures, risks, and benefits by [name] (author of this protocol). If they agree, they will sign an informed consent form. Only those participants who read and agree to the protocol and who sign the informed consent form will take part of the study, following the schedule described in Figure 1.

**Figure 1 F1:**
[figure not shown]
SPIRIT figure for the schedule of enrollment, interventions, and assessments.

### Participants

2.2

The subjects of this study will be included in the outpatient and hospitalized patients from the Department of DM Specialist of the Kailuan Majiagou Hospital (Tangshan City, Hebei Province), and meet the diagnostic criteria for T2DM and CHF.

#### Diagnostic criteria

2.2.1

1.Diagnostic criteria for T2DM. The diagnostic criteria adopted in accordance with the guidelines for the prevention and treatment of T2DM in China (2017 edition): those with typical DM symptoms, such as polyuria, polyphagia, excessive drinking, and unexplained weight loss; plasma glucose level ≥11.1 mmol/L (200 mg/dL); or fasting plasma glucose level ≥7.0 mmol/L (126 mg/dL); or fasting glucose is the critical value, glucose tolerance test, after meals 2 hours blood glucose level ≥11.1 mmol/L (200 mg/dL); exclude type 1 diabetes, special type diabetes, and gestational diabetes.2.Diagnostic criteria for CHF. We will refer to the diagnostic criteria for Framingham heart failure (Table 1). It mainly includes body weight loss ≥4.5 kg after treatment for more than 5 days. Those who meet 2 major criteria, or 1 major criterion, and 2 minor criteria can be diagnosed with CHF.3.Classification criteria for cardiac function. We will refer to the NYHA cardiac function grading standard of 1928 (Table 2).

**Table 1 T1:**
[figure not shown]
Diagnostic criteria of Framingham heart failure.

**Table 2 T2:**

NYHA cardiac function grading standards.

#### Inclusion criteria

2.2.2

This study will be conducted in China. Patients will be recruited from Plastic Surgery Departments of the Kailuan Majiagou Hospital. We will enroll participants based on the following inclusion criteria:

1.Comply with the diagnostic standards of western medicine T2DM and CHF.2.Cardiac function grading (grading) belongs to 2 to 4 patients.3.The age is between 45 and 85 years old.4.Those who have voluntarily signed the informed consent;

#### Exclusion criteria

2.2.3

Patients will be excluded if they meet the following criteria:

1.Patients with severe diseases such as malignant hypertension, severe arrhythmia, acute myocardial infarction, cerebrovascular accident, etc.2.Patients with acute infection, trauma, surgery, diabetic ketoacidosis, and hyperosmolar coma recently.3.Patients with severe primary diseases such as brain, liver, kidney and hematopoietic system, mental illness, and cognitive dysfunction.4.Patients with tumor and other organ failure.

#### Conditions for participants to suspend and withdraw from the clinical trial

2.2.4

Researchers participating in clinical trials should carefully record the reasons for the suspension of the trial and the relationship with the clinical trial. It is necessary to clearly record the unwillingness of the subjects to continue the clinical trials, put forward the reasons for withdrawing from the clinical trials, and record the evaluation indicators at the time of discontinuation in detail.

1.The main symptoms are not clear; the extended description of the current medical history is incomplete; the chief complaint or the description of the current medical history does not match the diagnosis of this disease.2.Incomplete records of tongue coating and pulse of TCM affect the syndrome judgment of this disease.3.The lack of or incomplete general information and physical and chemical index information affects the analysis of relevant data.

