### Interventions

2.3

Case information collection: We will collect inpatient records and outpatient cases of patients with T2DM and CHF admitted to Majiagou Hospital in Kailuan. We will fill in the case information collection form to collect a variety of clinical diagnosis and treatment information:

1.Basic information: medical record number, admission time, name, gender, age, etc.2.Brief medical history: symptoms, signs, tongue, pulse, medical history, course of T2DM, physical examination, diagnosis, etc.3.Auxiliary examination: including glycosylated hemoglobin (HbAlc), triglyceride, cholesterol, urine microalbumin, *N*-terminal pronatriuretic peptide (NTProBNP), left ventricular ejection fraction, liver and kidney function.

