The TCM holds that CHF combined with T2DM is a compound disease syndrome, and its pathogenesis is complicated and intertwined, and the syndrome types are complex and diverse.^[24]^ Due to the influence of DM factors, it has its own particularity. Modern medicine has increasingly perfected the understanding of the etiology, pathogenesis, energy metabolism, and other aspects of T2DM combined with CHF, and standardized treatment programs have made great progress. However, there are no special effective measures for the prevention and treatment of the disease, and there are certain limitations that cannot meet the growing health needs of patients.^[25]^ TCM treatment T2DM combined with CHF has flexibility and diversity. Compared with single-component chemical preparations, various components of TCM compound can cooperate with each other to play a therapeutic role. TCM belongs to multitarget, multichannel, and multilink comprehensive treatment.^[26]^ To achieve the purpose of controlling blood sugar, regulating blood lipids, preventing and treating myocardial fibrosis, and improving cardiac function. At present, there is no unified etiology, pathogenesis, and syndrome differentiation criteria for T2DM combined with CHF, and it is susceptible to subjective factors. Therefore, standardized, objective, and standardized research is needed to provide reference and guidance for clinical diagnosis and treatment. In this clinical study, we will screen no fewer than 500 cases that meet the inclusion criteria, collect clinical diagnosis, and treatment information, apply syndrome differentiation theory, extract syndromes, and establish a database. Then we will enter the relevant clinical indicators and syndrome information, statistical analysis of the data. This study will initially explore the distribution of TCM syndromes in T2DM patients with CHF and summarize the basic TCM pathogenesis of this disease.

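### Section 2.2.4 makes unclear or incomplete records grounds for withdrawing eligible patients, which can bias the syndrome distribution the study sets out to describe

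*Protocol article*

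**What the plan says.** Section 2.2.4 is headed "Conditions for participants to suspend and withdraw from the clinical trial" and stands apart from the exclusion criteria in section 2.2.3. It lists three conditions:

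- Item 1: "The main symptoms are not clear; the extended description of the current medical history is incomplete", and also where "the chief complaint or the description of the current medical history does not match the diagnosis of this disease". No qualifier is attached.
- Item 2: "Incomplete records of tongue coating and pulse of TCM affect the syndrome judgment of this disease".
- Item 3: "The lack of or incomplete general information and physical and chemical index information affects the analysis of relevant data". No list of items and no threshold is given.

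The same section asks investigators to record the reasons for suspension or withdrawal and the evaluation indicators at that time.

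Section 2.3 collects symptoms, signs, tongue and pulse, and a set of auxiliary tests "including glycosylated hemoglobin (HbAlc), triglyceride, cholesterol, urine microalbumin", NT-proBNP, ejection fraction, and liver and kidney function. Both inpatient and outpatient cases are taken. Section 2.4 reports counts as proportions or rates and relates syndromes to clinical indicators in a model.

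On numbers, the abstract says "we will collect at least 500 cases of type 2 diabetes with chronic heart failure" and the Discussion says "we will screen no fewer than 500 cases that meet the inclusion criteria". Neither refers to section 2.2.4.

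**The concern.** The study's main product is a distribution: what share of patients with type 2 diabetes and chronic heart failure show each syndrome. Its validity depends on who is in the denominator. The conditions in section 2.2.4 apply to patients who have met the inclusion criteria and signed consent, and they do not concern safety or a patient's wish to leave. The article describes one collection of case information, so withdrawal most naturally means that the case leaves the dataset.

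Two mechanisms follow. Under items 1 and 2, a patient can be removed because the symptom, history, tongue or pulse information is unclear or incomplete, and the syndrome is judged from that same information. The Introduction says that manifestations differ greatly by stage and that these patients differ from ordinary heart failure patients in their symptoms, so patients with unclear presentations belong to the target population. Under item 3, a patient whose syndrome can be judged may still be removed for a laboratory gap. Nothing in the article says that the syndrome distribution needs laboratory values.

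Bias from such selection does not shrink as more cases are collected.

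**Working it through.** **Inputs.** From the documents: a minimum of 500 cases (abstract and Discussion), with no derivation, precision target or loss rate, so there is no calculation to reproduce. Assumed, because the article gives no such figures: every prevalence, removal rate and completeness rate below.

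**1. Removal that differs by syndrome.** Let p be the true prevalence, r1 the share removed among patients with the syndrome and r0 the share removed among those without. Then

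observed = p(1 − r1) / [p(1 − r1) + (1 − p)(1 − r0)].

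For p = 0.50, r1 = 0.20, r0 = 0.10: 0.40 / (0.40 + 0.45) = 0.471. For r1 = 0.30: 0.35 / (0.35 + 0.45) = 0.4375.

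| True p | r1 / r0 | Observed | Shift (points) | Left of 500 |
|---|---|---|---|---|
| 50% | 10% / 10% | 50.0% | 0.0 | 450 |
| 50% | 20% / 10% | 47.1% | −2.9 | 425 |
| 50% | 30% / 10% | 43.8% | −6.3 | 400 |
| 50% | 10% / 30% | 56.3% | +6.3 | 400 |
| 30% | 20% / 10% | 27.6% | −2.4 | 435 |
| 30% | 30% / 10% | 25.0% | −5.0 | 420 |

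The shift can go either way, and equal removal gives none.

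**2. Dropping undetermined cases.** If 10% or 20% of patients cannot be classified and are dropped, a syndrome identified in 40% of all patients is reported as 0.40 / 0.90 = 44.4% or 0.40 / 0.80 = 50.0%.

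**3. Removal that differs by setting.** This biases the result only if prevalence also differs by setting. Assume half the patients are inpatients, prevalence is 50% in inpatients and 30% in outpatients, and 90% and 50% are retained. True prevalence is 40.0%. Observed is (0.5 × 0.9 × 0.5 + 0.5 × 0.5 × 0.3) / (0.5 × 0.9 + 0.5 × 0.5) = 0.300 / 0.700 = 42.9%.

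**4. Precision.** The 95% half-width is 1.96 × √[p(1 − p)/n]. At p = 0.5 it is 4.38 points for n = 500, 4.62 for 450, 4.90 for 400 and 5.24 for 350. Loss of numbers alone therefore matters little. The 6.3-point shift exceeds the half-width at its own n of 400 (4.90); the 2.9-point shifts do not exceed even the 4.38 points at n = 500.

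**5. The count of 500.** If it is taken before removals, losses of 5%, 10%, 20% or 30% leave 475, 450, 400 or 350. Keeping 500 analysable would need 500 / (1 − loss), rounded up: 527, 556, 625 or 715. If it is taken after removals, nothing is lost.

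**The case against.** The strongest defence is that section 2.2.4 is a record-quality check. Item 1 speaks of how the history is described and of a mismatch with the disease diagnosis, not with a syndrome pattern, and removing records that contradict the diagnosis protects validity. Items 2 and 3 can be read as applying only where the gap affects the syndrome judgment or the analysis. The study is exploratory, and the article gives no removal rates.

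Much of this stands, and it rules out three stronger readings:

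- A reader might infer that any missing laboratory item removes a patient, and compute that eight independent items at 95% completeness leave 0.95^8 = 0.663, or 332 of 500. The text does not state that rule. It ties item 3 to an effect on the analysis, and neither independence nor the 95% comes from the documents.
- A reader might infer that the analysed number falls below 500. The figure is a minimum. The Discussion wording leans towards a count before removals and the abstract does not settle it, so the number may fall below 500 but need not.
- A reader might infer that the result will mainly describe inpatients, because outpatients have fewer tests. The article gives neither completeness by setting nor the inpatient–outpatient mix.

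The defence does not remove the core problem. The part of item 1 on unclear symptoms and incomplete history is unqualified and goes beyond a check of the diagnosis. The qualifiers on items 2 and 3 come without a threshold, so removal is left to discretion. Nor is this a detail that can wait for an analysis plan, because the withdrawal rule is written into the protocol.

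**Conclusion.** The point holds as a stated rule that can bias the main result; it does not show that the result will be biased. Under the assumed removal rates, the prevalence of a syndrome shifts by about 2 to 6 points, and by nothing if removal is equal across syndromes. The larger shifts exceed the sampling error of 500 cases. The conclusion rests on reading withdrawal as removal from the analysed cases, which is the natural reading of section 2.2.4 but is not spelled out. Whether 500 is counted before or after removals is an ambiguity to settle, and its effect on precision is modest. This should be fixed but does not undermine the study as a whole. It is best done now, since section 2.6 says recruitment has not started and a case dropped with an incomplete record may be hard to recover.

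**What to change.** Amend section 2.2.4 and align the related text:

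- Stop using items 1 to 3 as withdrawal conditions. The one exception is a record showing that the diagnostic criteria for type 2 diabetes or chronic heart failure are not met; handle that as ineligibility.
- Keep every eligible, consented patient in the denominator of the syndrome distribution, with an undetermined-syndrome category for those whose symptom, history, tongue or pulse record does not allow a judgment.
- Treat missing laboratory values as missing only in the analyses that use them. The method for doing so can be left to the analysis plan.
- Report undetermined and incomplete cases by reason and by inpatient or outpatient setting. The reasons are already to be recorded under section 2.2.4.
- State, in the same words in the abstract and the Discussion, whether the minimum of 500 is counted before or after removals.

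The cost is a change of protocol wording and a little more analysis. An undetermined category makes the results table slightly less tidy.

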### Interventions

2.3

Case information collection: We will collect inpatient records and outpatient cases of patients with T2DM and CHF admitted to Majiagou Hospital in Kailuan. We will fill in the case information collection form to collect a variety of clinical diagnosis and treatment information:

1.Basic information: medical record number, admission time, name, gender, age, etc.2.Brief medical history: symptoms, signs, tongue, pulse, medical history, course of T2DM, physical examination, diagnosis, etc.3.Auxiliary examination: including glycosylated hemoglobin (HbAlc), triglyceride, cholesterol, urine microalbumin, *N*-terminal pronatriuretic peptide (NTProBNP), left ventricular ejection fraction, liver and kidney function.

